### Statistical analysis plan

SPSS v22.0 will be used for statistical analyses. Primary analyses will be conducted on the Intention-To-Treat (ITT) sample. Missing data will be inspected and handled via full information maximum likelihood (FIML) or multiple imputations (MI) as appropriate.

The primary outcome is change in HDRS scores from baseline to post-treatment (8 weeks). For primary and secondary outcome measures, repeated measures ANOVAs will be computed to examine pre-post treatment differences between groups.

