**Methods:**

A total of 310 participants with major depression disorder (MDD) will be recruited at four different mental-health facilities in Spain. Participants will be randomly allocated to one of two study arms: iFightDepression (iFD) tool + TAU vs. internet-based psychoeducation + TAU. Both interventions last for 8 weeks and there is a 12 weeks follow up. The primary outcome measure is changes in depressive symptoms assessed with the Hamilton Depression Rating Scale. Additionally, pre-post interventions assessments will include socio-demographic data, a brief medical and clinical history and self-reported measures of depressive symptoms, quality of life, functional impairments and satisfaction with the iFD tool.

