## Methods

### Design

We designed an 8-week, double-blind, randomized controlled trial, with two treatment arms: iFightDepression tool + TAU and internet-based psychoeducation + TAU. Participants will be randomly allocated (1:1) after the first assessment visit. Randomization will be performed electronically by an independent study researcher. Participants in both treatment arms will be followed via internet during a 12-week period.

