### Procedure

Eligible participants will be identified through the different sites by a case manager, mainly, by the participant’s general practitioner. However, other professionals (i.e., psychiatrist, psychologist or community mental health nurses) with experience in the assessment and diagnosis of depression would be also able to refer participants to the study. These professionals will verify inclusion/exclusion criteria and will inform patients about the study. Participants who confirm their interest in participating, will be contacted by phone within 1 week to schedule the first assessment visit (face-to-face). Each site will designate a highly trained psychologist who will conduct the first face-to-face visit in order to confirm that participants met inclusion/exclusion criteria and to obtain the written informed consent. Participant’s assessment will be recorded in the electronic Case Report Form (e-CRF). In this assessment visit, and regardless of the treatment arm the patient will be assigned to, the second face-to-face assessment visit (week 8) will be booked. Randomization to one of the two conditions (i.e., iFightDepression tool + TAU or internet-based psychoeducation + TAU) will be electronically performed by the e-CRF once the patient data is introduced. The researcher who conducts assessment visits will remain blind to participant’s allocation. After the first visit, participants in both arms will received an email with instructions to be followed. The intervention group will receive instructions to create an account and to work within the iFD tool. In addition, the intervention group will receive a telephone call to make sure that participants activated successfully their user accounts. Then, they will be contacted bi-weekly by a mental health professional (specialized nurse or psychologist), to work through the material and to provide technical support). During the 8 weeks of the trail all participants will be follow-up by e-mail in order to complete the PHQ-9 and RDQ. Participants will have to complete the PHQ-9 and the RDQ again at week 12. The study protocol was developed in accordance with the SPIRIT (Standard Protocol Items: Recommendations for Interventional Trials) guidelines [17]. A flowchart of participants is shown in Fig. 1.

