## Discussion

The present study aims at evaluating the efficacy of an internet-based self-management tool for moderate to mild depression compared with internet-based psychoeducation. Confirming the efficacy of the iFightDepression tool will entail important implications. As IFD could be easily prescribed it could potentially reach patients that usually remain untreated or have to wait for long-periods to receive psychological treatment. In addition, the availability of the both interventions in three different languages (Spanish, Catalan and Basque) aims at facilitating participant’s adherence. A strength of our study is that the recruitment will mainly take place in general practices, were patients with mild to moderate depression symptoms are often treated.

The risk of dropout constitutes one of the potential major obstacles of our study. We’ve tried to mitigate this by expanding our recruitment area to public health-care facilities located in three large areas of Spain (Catalonia, Madrid and Basque Country) and by providing specific language versions of the iFD tool and the psychoeducation web-page. As commented before, the design of our study privileges a naturalistic approach and therefore, participants will be recruited from primary care facilities in which most patients with mild/moderate symptoms of depression are visited and participants with concomitant ant depressive medication will be allowed in the study. Considering that the effects of the concomitant medication may impact our findings, a sub-analysis evaluating the potential effects of antidepressant will be conducted and participants will be excluded from the study if drastic changes in their medication took place during the study period.

In summary, the present study aims to provide evidence in regards to iFD tool as an add-on approach for individuals presenting mild to moderate symptoms of depression. Counting on a tool like iFD will facilitate its use in the public health care system, representing a treatment approach that can potentially reach a large amount of patients avoiding long waiting lists.

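### The pre-post ANOVA stated for secondary outcomes uses two of the six scheduled PHQ-9 and RDQ assessments and gives no arm comparison at follow-up; the follow-up date also has no single origin

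*Protocol article*

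**What the plan says.** The Statistical analysis plan section of the protocol article fixes the primary endpoint ("The primary outcome is change in HDRS scores from baseline to post-treatment (8 weeks") and then gives a single efficacy method for everything: "For primary and secondary outcome measures, repeated measures ANOVAs will be computed to examine pre-post treatment differences between groups". On missing values it says: "Missing data will be inspected and handled via full information maximum likelihood (FIML) or multiple imputations (MI) as appropriate". The Discussion adds one further analysis: "a sub-analysis evaluating the potential effects of antidepressant will be conducted".

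Table 2, under Study measures, marks PHQ-9 and RDQ in all six columns. The Procedure section agrees: "During the 8 weeks of the trail all participants will be follow-up by e-mail in order to complete the PHQ-9 and RDQ", followed by "Participants will have to complete the PHQ-9 and the RDQ again at week 12".

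The length or date of follow-up is described in four places: the Abstract ("Both interventions last for 8 weeks and there is a 12 weeks follow up"), the Design section ("Participants in both treatment arms will be followed via internet during a 12-week period"), the Procedure sentence just quoted, and the last column heading of Table 2, which names a 12-week follow-up without saying when the 12 weeks start.

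**The concern.** A pre-post contrast suits an outcome measured once before and once after treatment. PHQ-9 and RDQ are not such outcomes, yet the article expressly assigns them the same method as the rest. The interim scores therefore have no stated role in estimating the treatment effect. The follow-up visit, at which nothing else is measured, has no stated comparison between arms.

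At stake is the secondary evidence on the course of self-reported symptoms and on whether any difference persists after the intervention ends. A persistence result also needs a date: a difference 4 weeks after treatment and a difference 12 weeks after treatment answer different questions. If sites read the text differently, the last visit would mix the two.

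**Working it through.** The plan gives no figure to reproduce on this point, and the sample size of 310 does not enter. The check is a count of the schedule and a comparison of dates.

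**1. Schedule against stated analysis (Table 2 and Statistical analysis plan)**

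- HDRS, EuroQol-5D, FAST: baseline and post-intervention, 2 times. A pre-post analysis uses 2 of 2.
- PHQ-9: baseline, weeks 2, 4, 6, post-intervention, follow-up, 6 times. A pre-post analysis uses 2 of 6.
- RDQ: the same six times. A pre-post analysis uses 2 of 6.

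Assessments of PHQ-9 and RDQ outside the stated contrast: 6 − 2 = 4 for each, namely weeks 2, 4, 6 and follow-up. The follow-up column of Table 2 is marked for PHQ-9 and RDQ only, so no outcome has a stated between-arm comparison at that visit. The antidepressant sub-analysis in the Discussion is not described as using the extra visits.

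**2. Follow-up date**

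- Procedure: the second face-to-face visit is placed at week 8, so weeks are counted from the start. Week 12 on that count is 12 − 8 = 4 weeks after treatment.
- Abstract: 8 weeks of intervention and a 12-week follow-up. Read as consecutive periods, this is 8 + 12 = week 20, or 12 weeks after treatment.
- Design: a 12-week period followed via internet, with no start given.
- Table 2: the interim columns are labelled by study week, but the last column is labelled as a 12-week follow-up, with no origin.

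The two readings differ by 20 − 12 = 8 weeks.

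**3. Feasibility of the replacement**

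PHQ-9 and RDQ each have 6 − 1 = 5 post-baseline visits. An unstructured covariance matrix then has 5 × 6 / 2 = 15 parameters, which is modest for 310 planned participants.

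**The case against.** The strongest reply is that this is a condensed article. How secondary questionnaires are modelled over interim and follow-up visits is commonly left to a full protocol or SAP, neither of which is shown, and silence is not an error. That would settle the matter if the article were silent. It is not: it names a method, says that it covers the secondary outcomes, and describes it as pre-post. The point is the poor fit of that stated choice.

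Other parts of the reply stand, and they limit the point:

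- **The extra visits are worthless or discarded.** A reader might infer this, but the article does not say so. Interim scores could inform FIML or multiple imputation of a missing week-8 score, although that use is not specified.
- **Participants who miss one online form would be dropped.** This would follow from a complete-case ANOVA over all six times. The article plans neither that analysis nor complete-case handling; it names an ITT sample with FIML or multiple imputation. No loss-of-participants figure can be charged to the plan.
- **The trial cannot show whether a benefit lasts.** This goes too far. Both questionnaires are due at follow-up in both arms, so a comparison is possible; the stated analysis does not supply it.
- **The follow-up dates flatly contradict each other.** The Abstract, Design and Table 2 can all be read as 12 weeks from baseline, which agrees with the Procedure. That reading strains the Abstract sentence, and no section states it, so the ambiguity is real but is not a proven contradiction.

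**Conclusion.** The point holds as a mismatch between a stated method and the schedule. For PHQ-9 and RDQ the stated efficacy analysis covers 2 of 6 assessments and provides no arm difference at follow-up. This rests on taking the pre-post wording at face value for the secondary outcomes, as the sentence itself directs. An unseen SAP may already go further, in which case the article's sentence needs aligning with it.

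The follow-up date is a smaller, separate inconsistency. The text supports either 4 or 12 weeks after treatment, and the sections must be reconciled.

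The primary analysis is untouched, since HDRS has no interim or follow-up assessment. The change is worth making because it secures the secondary results at little cost; the main conclusion of the trial does not depend on it.

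**What to change.** 1. For PHQ-9 and RDQ, replace the pre-post repeated measures ANOVA with a likelihood-based linear mixed model. Outcome: scores at all five post-baseline visits. Fixed effects: baseline score, arm, visit and arm-by-visit interaction. Covariance: unstructured. Report the arm difference with its confidence interval at week 8 and at follow-up. The model uses every observed post-baseline score by maximum likelihood, which is in keeping with the FIML option already named.

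2. Reconcile the Abstract, Design, Procedure and Table 2 to one follow-up date with a stated origin, for example by giving it in weeks from randomisation. Which date applies is for the investigators to state.

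Cost: a revised analysis sentence, one schedule clarification and some extra analysis work. The visits and questionnaires are already in the schedule, so no additional data collection is required.

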### Study participants

A total of 310 participants with major depressive disorder (MDD) diagnosis will be included in the study. Diagnosis will be made according DSM-IV-TR criteria and participants will be recruited from different mental health services (i.e., Red de Salud Mental de Guipúzkoa, Hospital del Mar, Hospital de la Santa Creu i Sant Pau, Hospital Parc Taulí and Hospital Universitario de la Princesa) and primary care facilities in their catchment areas. Sample size was established in order to detect an effect size of d = 0.2 with 95% power (SE = 0.5) and assuming a conservative correlation coefficient between pre-post measures of 0.5 and a drop-out of 20%. Sample size was calculated using G*Power 3.1.7 software.

Individuals meeting the following criteria will be eligible: 1) Participants of both genders 18 years old and older, 2) MDD diagnosis according to DSM-IV-TR criteria with mild-moderate symptoms according to the CGI-severity (scores ≤4), 3) minimum knowledge of internet use and availability of an internet device (tablet, computer, smartphone) and 3) given written informed consent. Exclusion criteria are: 1) suicidal ideation assessed by the HDRS and/or clinical interview, 2) psychotic symptoms related or not related to a mood disorder, 3) severe comorbidity axis I and axis II diagnosis, 4) currently receiving standard face-to-face CBT.

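### With HDRS measured only at baseline and week 8, the planned repeated-measures ANOVA is a change-score t-test: valid, but less precise than adjusting week-8 HDRS for baseline HDRS

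*Protocol article*

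**What the plan says.** The Statistical analysis plan section of the protocol article sets the primary outcome as the change in HDRS between baseline and the end of treatment at 8 weeks. For this outcome and the secondary ones it names the test: "repeated measures ANOVAs will be computed to examine pre-post treatment differences between groups". No section mentions ANCOVA or baseline HDRS as a covariate. Missing data are to be handled by FIML or multiple imputation.

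Table 2 (Study measures) shows HDRS at the baseline and post-intervention visits only. EuroQol-5D and FAST follow the same two-visit pattern. The Design section says "Participants will be randomly allocated (1:1) after the first assessment visit", so baseline HDRS is recorded before allocation.

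The sample-size paragraph in Study participants gives d = 0.2 and 95% power, "assuming a conservative correlation coefficient between pre-post measures of 0.5", and 20% dropout, for a total of 310.

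**The concern.** A change score subtracts the whole of the baseline value, which amounts to fixing the slope of week-8 HDRS on baseline HDRS at 1. If the SDs at the two visits are equal, the plan's own correlation of 0.5 implies a slope of 0.5. The change score then takes off too much and carries baseline noise into the treatment estimate. Baseline adjustment estimates the slope instead of assuming it.

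What is at stake is precision on the primary outcome. The change-score estimate also responds more to any chance difference between the arms at baseline. Neither threatens the type I error, but both can be avoided with data the trial already collects.

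**Working it through.** **Inputs.** From Study participants: N = 310, dropout 20%, rho = 0.5, d = 0.2, power 95%. From Design: 1:1 allocation. Completers: 310 × 0.8 = 248, or 124 per arm. Two-sided alpha 0.05 is assumed, because the article states none. It gives no HDRS SDs either, so results are in units of the baseline SD, and k denotes the week-8/baseline SD ratio.

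**The plan's own figure.** "Sample size was calculated using G*Power 3.1.7 software". Of the variants tried, the one closest to 310 enters 0.2 as Cohen's f in the between-factors test with two measurements: lambda = f² × N × 2/(1 + rho). This needs N = 246, and 246/0.8 = 307.5, or 308. Reading 0.2 as d (f = 0.1) in the group-by-time test needs 328, and 328/0.8 = 410. The basis of 310 is a separate question. The variance comparison below depends only on rho and k.

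**Equivalence.** With two groups and two waves, the group-by-time F is the square of the t statistic on change scores. Two simulated data sets confirm it: 12.8559 for both statistics in one, 6.0756 for both in the other.

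**Variance, general form** (baseline SD = 1):
- Change score: 1 + k² − 2·rho·k
- Week 8 adjusted for baseline: k²(1 − rho²)
- Difference: (1 − rho·k)², which cannot be negative. It is zero only when rho·k = 1, that is, when the true slope really is 1.

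**Equal SDs (k = 1).** The variances are 2(1 − rho) and 1 − rho². Their ratio is (1 + rho)/2, so the reduction is (1 − rho)/2.

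| rho | Change | Adjusted | Reduction |
|---|---|---|---|
| 0.3 | 1.40 | 0.91 | 35% |
| 0.5 | 1.00 | 0.75 | 25% |
| 0.7 | 0.60 | 0.51 | 15% |
| 0.8 | 0.40 | 0.36 | 10% |

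A simulation with 124 per arm at rho = 0.5 gave 24%. The small gap reflects estimation of the slope and simulation error.

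**Unequal SDs at rho = 0.5 (assumed ratios).**

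| k | Change | Adjusted | Reduction |
|---|---|---|---|
| 0.8 | 0.84 | 0.48 | 43% |
| 1.0 | 1.00 | 0.75 | 25% |
| 1.2 | 1.24 | 1.08 | 13% |
| 1.5 | 1.75 | 1.6875 | 4% |

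**Power at the stated d = 0.2, in raw SD units** (rho = 0.5, k = 1, 248 completers). The noncentrality is 248 × 0.2²/4 = 2.48 for the change score and 2.48/0.75 = 3.31 after adjustment. Power is 34.8% and 44.1% respectively.

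**Difference detectable with 95% power.** (1.960 + 1.645) × √(2/124) = 0.458 SD by change score, and (1.960 + 1.645) × √(1.5/124) = 0.396 SD after adjustment. Equivalently, 248 adjusted completers carry the information of 248/0.75, about 331, analysed by change score.

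**Chance baseline imbalance.** Given a baseline difference D between the arms, the change-score estimate is shifted in expectation by (rho·k − 1)·D, which is −0.5·D at rho = 0.5 and k = 1. One standard error of D is √(2/124) = 0.127 SD, so the shift is 0.5 × 0.127 = 0.064 SD in size. Averaged over randomizations it is zero.

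**The case against.** The strongest reply is that nothing here is invalid. Under 1:1 randomization the change-score contrast is unbiased, holds its error rate and matches the declared outcome. That stands. A reader might infer from the imbalance argument that the planned estimate is biased. It is not: the shift is conditional on the imbalance that happens to occur and averages to zero.

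Second, the 25% is not a property of the trial. It needs equal SDs. Entry is limited to CGI-S of 4 or below and suicidal ideation is excluded, which may narrow the baseline spread, push k above 1 and shrink the gain. The plan also calls 0.5 conservative. For a change outcome that suggests a true correlation of at least 0.5 and hence, with equal SDs, a gain of 25% or less. Both points stand, and they are why a range is given.

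Third, a condensed article may leave covariates to the full protocol or the SAP. That is fair for site or antidepressant use, and their absence is not criticised here. It does not cover the choice of test, which the article makes. Nor does FIML or multiple imputation supply the adjustment, since these deal with missing values.

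Two stronger readings are tempting. One is that the trial would test the group main effect of the ANOVA, which averages in the pre-treatment score. The way 310 is most nearly reproduced might suggest this, but the analysis section ties the test to pre-post differences on a change outcome, which is the group-by-time term. The other is that adjustment would restore the planned power. At the stated d = 0.2 it does not.

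**Conclusion.** The point holds as one of efficiency. The named primary test is a valid change-score comparison, and baseline adjustment is at least as precise in large samples whatever rho and the SD ratio turn out to be. The variance reduction is 25% if rho is 0.5 and the SDs are equal, 15% if rho is 0.7 with equal SDs, and about 4% to 43% at rho 0.5 over assumed SD ratios from 1.5 down to 0.8. Power at d = 0.2 goes from about 35% to 44% with 248 completers, rho 0.5, equal SDs and two-sided alpha 0.05. The change is worth making because it needs no new data. It does not settle the separate sample-size question.

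**What to change.** In the Statistical analysis plan section, and in any full SAP, name as primary an ANCOVA of week-8 HDRS on arm with baseline HDRS as covariate, or the equivalent constrained longitudinal model. Report the adjusted mean difference with its 95% CI. The declared outcome can stay as it is: with baseline in the model, the arm coefficient is the same whether week-8 HDRS or the change is the dependent variable. Use the same form for EuroQol-5D and FAST, each with its own baseline. Further covariates, such as site or baseline antidepressant use, are optional and do not follow from this argument. Record the change before outcome data are examined by arm.

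The cost is a wording change and one residual degree of freedom (246 to 245 with 248 completers). No patients, visits or measures are added.

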## Discussion

The present study aims at evaluating the efficacy of an internet-based self-management tool for moderate to mild depression compared with internet-based psychoeducation. Confirming the efficacy of the iFightDepression tool will entail important implications. As IFD could be easily prescribed it could potentially reach patients that usually remain untreated or have to wait for long-periods to receive psychological treatment. In addition, the availability of the both interventions in three different languages (Spanish, Catalan and Basque) aims at facilitating participant’s adherence. A strength of our study is that the recruitment will mainly take place in general practices, were patients with mild to moderate depression symptoms are often treated.

The risk of dropout constitutes one of the potential major obstacles of our study. We’ve tried to mitigate this by expanding our recruitment area to public health-care facilities located in three large areas of Spain (Catalonia, Madrid and Basque Country) and by providing specific language versions of the iFD tool and the psychoeducation web-page. As commented before, the design of our study privileges a naturalistic approach and therefore, participants will be recruited from primary care facilities in which most patients with mild/moderate symptoms of depression are visited and participants with concomitant ant depressive medication will be allowed in the study. Considering that the effects of the concomitant medication may impact our findings, a sub-analysis evaluating the potential effects of antidepressant will be conducted and participants will be excluded from the study if drastic changes in their medication took place during the study period.

In summary, the present study aims to provide evidence in regards to iFD tool as an add-on approach for individuals presenting mild to moderate symptoms of depression. Counting on a tool like iFD will facilitate its use in the public health care system, representing a treatment approach that can potentially reach a large amount of patients avoiding long waiting lists.

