For the purpose of this study and to facilitate the recruitment, the IFD tool is available in three languages: Spanish, Catalan and Basque, and patients are allowed to choose among versions according to their language preferences. Participants can access the PHQ-9 at any time, to assess their depression symptoms. A guide for interpreting the PHQ-9 scores is provided. If the patient responds positively to the item regarding suicide (i.e., “Thoughts that you would be better off dead or of hurting yourself in some way”) a message recommending seeking for emergency care will appear on the top of the screen. In addition, emergency contacts for Spain are listed on the website. The use of IDF tool is complementary to TAU which consists of monthly visits with the GP and pharmacological treatment with an ISRSS if needed.

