#### Active control group (internet-based psychoeducation + TAU)

Internet-based psychoeducation consists of a webpage containing information about MDD and healthy habits. This webpage (www.ifightdepression.com) was also designed by the EAAD consortium, and unlike the tool, workshops and tasks are lacking. The psychoeducative content of this website is restricted to information regarding healthy habits (healthy eating, physical activity, positive social contact and daily organization). In addition, information on the following topics is included: what is depression, signs and symptoms, diagnosing depression, subtypes of depression, brain function in depression, causes and an overview of depressions treatment (both pharmacological and psychological). Participants on this condition can also complete the online PHQ-9. This is an open-access webpage (i.e., a username and password are not required). Participants allocated to this condition will receive an e-mail with the page link and will be instructed to navigate freely throughout their content. As in the intervention group, TAU consists of monthly visits to the GP together with pharmacological treatment (if needed).

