### Study measures

Different types of variables will be collected (see Table 2) including socio-demographic characteristics of the sample (i.e., gender, age, ethnic group, marital status, living arrangements, educational level, employment status and annual income) and an exhaustive clinical history [i.e., age at MDD onset, number of previous MDD episodes, days in inpatient hospitalization (if applied), axis I and axis II diagnosis, and current pharmacological treatment].

**Table 2 Tab2:** Measures used by study period

Measure	Baseline assessments (Face to face)	Week 2 (Online)	Week 4 (Online)	Week 6 (Online)	Post-intervention assessment (Face to face)	12 weeks FU (online)
Demographic information (gender, age, marital status, etc.)	x					
Medical/Psychiatric History	x				x	
MINI (depression and suicide risk sections)	x				x	
Primary outcome measure:						
-HDRS	x				x	
Secondary outcome measure:						
-PHQ-9	x	x	x	x	x	x
-CGI-S					x	
-RDQ	x	x	x	x	x	x
-EuroQol-5D	x				x	
-FAST	x				x	
-Ad hoc satisfaction Questionnaire					x	

*Note*: *MINI* Mine-international Neuropsychiatric Interview, *HDRS* Hamilton Depression Rating Scale, *PHQ-9* Patient health Questionnaire, *CGI-S* Clinical Global Impression-Severity, *CGI-I* Clinical Global Impression-Improvement, *RDQ* Remission from Depression Questionnaire, *FAST* Functioning Assessment Short Test

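### The antidepressant sub-analysis does not say whether baseline or on-trial use defines its groups; it should be an exploratory arm-by-baseline-status interaction

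*Protocol article*

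**What the plan says.** All references are to the protocol article.

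- **Discussion.** Medicated patients may enter: "participants with concomitant ant depressive medication will be allowed in the study". The analysis promised in response: "Considering that the effects of the concomitant medication may impact our findings, a sub-analysis evaluating the potential effects of antidepressant will be conducted". The same sentence goes on: "participants will be excluded from the study if drastic changes in their medication took place during the study period".
- **Description of the interventions.** In the iFD arm, usual care "consists of monthly visits with the GP and pharmacological treatment with an ISRSS if needed". In the control arm, "TAU consists of monthly visits to the GP together with pharmacological treatment (if needed".
- **Study measures.** The clinical history covers "axis I and axis II diagnosis, and current pharmacological treatment". Table 2 marks medical/psychiatric history at baseline and at the post-intervention visit.
- **Design.** Only iFD versus psychoeducation is randomised, 1:1.
- **Statistical analysis plan.** The primary outcome is HDRS change from baseline to week 8, analysed by intention to treat with repeated measures ANOVA. The antidepressant sub-analysis is not mentioned there.

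**The concern.** As worded, the object of the sub-analysis is the effect of the drug. The trial's question, under Study objectives, is whether iFD adds to usual care. Nobody is randomised to an antidepressant. Patients may enter on one, and others may be given one during the 8 weeks because a GP judges it necessary. The Background says that most GPs tend to prescribe antidepressants, and the Procedure makes GPs the main source of referrals, so exposure may be common.

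Two problems follow if on-trial use forms the groups. First, those who receive a drug differ in prognosis from those who do not. Second, use after randomisation can depend on the arm: if iFD works, fewer iFD patients may be prescribed a drug, and the groups are then partly a result of allocation.

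What is at stake is the reading of a secondary analysis that is meant to show how far medication accounts for the findings. A false drug benefit or a false drug harm could be taken from it.

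**Working it through.** The document gives no size, power or effect for this sub-analysis, so there is no figure to reproduce. The check is an illustration of bias, then the precision of the alternative.

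**1. Bias when the true drug effect is zero**

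Inputs:
- Pre-post correlation 0.5 (Study participants).
- Baseline and week-8 scores y0 and y1 in SD units, SD 1 at each visit (scaling).
- Prescribing model (assumption): log-odds of starting = -0.85 + g·x, with g = 0.5 to 1.0. About one third of patients start (31% to 33%).
- x is the severity that drives prescribing, under three assumed patterns.

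Starters minus non-starters, in SD; negative means that starters look better. Each range runs from g = 0.5 to g = 1.0.

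| What drives starting | Change score | Week-8 score | Week 8 adjusted for baseline |
|---|---|---|---|
| Baseline severity, x = y0 | -0.24 to -0.42 | +0.24 to +0.42 | 0.00 |
| Midpoint, x = (y0 + y1)/2 | 0.00 | +0.36 to +0.65 | +0.18 to +0.36 |
| Mainly poor course, x = 0.25·y0 + 0.75·y1 | +0.12 to +0.22 | +0.42 to +0.75 | +0.28 to +0.52 |

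The first row is regression to the mean. If starters are D worse at baseline, the expected week-8 gap is 0.5·D and the gap in change is (0.5 - 1)·D = -0.5·D. Baseline adjustment removes it. In the third row starting reflects course after baseline, which baseline adjustment cannot remove. For scale, the trial is designed around d = 0.2.

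**2. Dependence of on-trial use on arm**

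Two simulations assumed HDRS SD 6, starts when a mid-course score exceeds 16, and an iFD effect of -1.2 points (0.2 × 6). Start rates were 13.4% (iFD) against 15.1% (control) in one and about 16.5% against 18.5% in the other, a difference of roughly 2 percentage points. The dependence is there but small under these assumptions.

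**3. Precision of the arm-by-baseline-status interaction**

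Completers: 310 × 0.8 = 248. The SD of change is √(2 × (1 - 0.5)) = 1 SD. With a share q medicated at baseline (assumed 30% to 70%) and equal arms:

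SE = √[4/(248q) + 4/(248(1 - q))]

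- q = 0.5: √(0.0323 + 0.0323) = 0.254; detectable at 80% power, 2.80 × 0.254 = 0.71 SD.
- q = 0.3 or 0.7: √(0.0538 + 0.0230) = 0.277; 2.80 × 0.277 = 0.78 SD.

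With no true interaction, the simulated mean of this contrast was -0.01 to 0.00, even when baseline use depended on baseline severity.

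**4. Gain from a baseline covariate**

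Assume that a share p (20% to 50%) recently started a drug and improves δ (2 to 4 points) more, with residual SD 6. Variance explained = p(1 - p)δ² / [36 + p(1 - p)δ²].

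- Low end: 0.16 × 4 = 0.64; 0.64/36.64 = 1.7%.
- High end: 0.25 × 16 = 4; 4/40 = 10%.

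The standard error of the arm effect falls by a factor of √(1 - 0.017) = 0.99 to √(1 - 0.10) = 0.95, that is by about 1% to 5%.

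**The case against.** The strongest objection is that the error is not on the page. One Discussion clause names a sub-analysis and no exposure definition, contrast or model. Its opening worry is about the trial's findings, which are the iFD comparison, so a check of the iFD effect by baseline medication fits the words too. This is a condensed article, and such detail may sit in a statistical analysis plan that is not shown. This stands to the extent that a user versus non-user comparison is a reading, not a stated plan. It does not remove the point: the stated object is still the drug's effect, and the article leaves open on-trial use as the grouping, which its own description of usual care makes unsafe.

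Stronger readings that a reader might infer, and why they fail:

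- *The sub-analysis will give a wrong answer, and will hide or reverse a drug benefit.* No method is stated, and the table above shows bias in either direction or, for change scores under the midpoint pattern, none.
- *Start dates are not recorded.* The e-CRF is not shown, and the article calls the clinical history exhaustive.
- *Recent medication is the largest competing source of 8-week change.* Nothing supports this; the illustration gives 2% to 10% of variance.
- *The primary result is compromised.* Randomisation protects the arm comparison whatever the medication mix.

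A further objection is that the exclusion for drastic changes may remove on-trial starters. It might, but the article does not define drastic or say whether a new start counts. It is also a selection made after randomisation. It does not rescue the sub-analysis, and it sits badly with the intention-to-treat statement.

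**Conclusion.** The point holds in a conditional form. The article commits to a sub-analysis of a non-randomised exposure that may begin after randomisation, without fixing which use counts. If users are compared with non-users, or on-trial starts define the groups, confounding by indication and natural course can produce a false benefit (0.24 to 0.42 SD in change) or a false harm (0.12 to 0.22 SD in change; 0.28 to 0.52 SD after baseline adjustment) with no drug effect at all. These sizes rest on an assumed prescribing model; only the correlation of 0.5 comes from the document.

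Baseline status is not randomised either, so its main effect is not a drug effect. What randomisation does protect is the iFD contrast within baseline strata. The matter is secondary: the primary comparison is not biased by it, and the gain there from a baseline covariate is in precision only.

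**What to change.** 1. Define the factor from baseline status only: no antidepressant; recently started or changed, with the window fixed in advance; unchanged. Use the current treatment already collected, and add a start or change date if the e-CRF does not hold one.
2. Include this factor as a covariate in the primary HDRS model.
3. Report the sub-analysis as an exploratory arm-by-baseline-status interaction, with the iFD effect and its interval in each stratum. Do not present it as an effect of the drug.
4. Describe antidepressant starts during the trial by arm, as a post-randomisation outcome and not as a grouping variable.
5. Reconcile the Discussion's exclusion for drastic medication changes with the intention-to-treat statement in the Statistical analysis plan section: say what counts as drastic, and whether those patients' data stay in the primary analysis.

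The cost is analysis wording and at most one date field. The drawback is imprecision. With two strata and 248 completers, only a difference of about 0.7 to 0.8 SD in the iFD effect is detectable at 80% power, and three strata will be less precise, so a null interaction must not be read as evidence that medication makes no difference. A randomisation stratum for this factor is not needed.
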